### Arms and interventions

#### Experimental group intervention

**NE**uroplasticity-**P**rinciples-based **SE**nsory-**R**ehabilitation (**NEPSER**) Protocol is based on the key principles of neuroplasticity [7, 14] established in relation to the rehabilitation of stroke subjects. In order to enhance the impaired sensory deficit, active training of the specific sensory modalities will be imparted. Similar to the motor rehabilitation regimes, the repetitiveness of sensory experiences will be provided by adequate training time. The sensory training will be imparted by utilizing visuo-perceptual, cognitive, motor, and functional tasks. Variety of meaningful tasks of daily life having sensory demand in addition to the motor will also be incorporated.

The following guidelines will be utilized while executing the experimental intervention:
Maximum duration of the protocol will be 120 min with 20–25 min for each sensory modality with maximum of 5 min for each level of intervention and intermittent rest period. In case, there is no impairment of a certain modality, the training time for that modality will be equally distributed to other impaired ones, with a maximum of 40 min for each.The order of modality training will be in random order in each session.The training will be imparted in order of lower level of therapy to the higher ones.Sharp sensory stimulus will be in safer limits.Mirror therapy (MT) activities will be graded from unilateral (non-paretic limb performance) to bimanual (simultaneously moving on both sides).MT protocol will be provided as per the published study (Arya et al. 2018) [15]Sensory imagination (2 min) for each stimulus will be provided to prior to every sub-session of training.Other activities will be graded from bilateral to unilateral (constraining the non-paretic limb).Gradation of activities will also be done from visual feedback to vision occluded.Variety of sensori-motor objects / activities should be utilized for imparting the intervention.Auditory cues, guidance, motivation will be provided by the therapist as per the requirement.The constraint will be provided using a sling for sensory-functional training for higher stage patients.Therapy for different type of sensory deficits will be provided separately.Therapy for sensory deficit will be provided as per the motor recovery stage of the hand.Levels of intervention will range from neural activation using mirror therapy and sensory imagination to active perception of stimuli and sensory motor usage in non-functional to meaningful functional items.Therapy will be provided in distraction free and calm environment.Blindfolding the subject during the therapy session will be performed as per the need.The therapy may be modulated as per the extent of sensory deficit of specific type.Two minutes rest break after training of each modality will be providedVariety of items with similar texture / therapeutic value will be used.Home program comprising of functional touch of variety of meaningful objects/ sensation will be provided throughout the day for 2–3 h during the entire 8-week.The home program will be supervised through a log book maintained by patient/care taker regarding the sensory-functional usage.

Levels of therapy:

The NEPSER protocol will be imparted in a sequence of 4 levels, ranging from neural activation to functional usage of different sensory modalities.
Level I: Neural Activation
Mirror therapy (illusion of the normal sensory perception using mirror-box therapy);Sensory imagery (imagery of the normal sensory perception)These techniques may enhance the neural activation of the sensory cortex. The activation will provide a reasonable base for active sensory training. The perception such as various texture, size, shape, and objects will be used.Level II: Active Sensory-Training
The active sensory training for modalities such as tactile awareness and localization, texture recognition, and stereognosis will be provided by prolong-duration, meaningful and bimanual sensory perception.Level III: Sensori-Motor therapy
Motor therapy will be provided using specific stimuli (textured, shape) during activities.Level IV: Sensory-Functional therapy
Prolong-duration functional therapy using various meaningful shapes, sizes and textured objects of daily use will be provided.

The detail of execution of the experimental intervention is provided in Table 1. The regime will be imparted for 40 sessions, each 2 h, 5 sessions / week across 2 months. The assessments will be carried out at baseline, 8-week post-intervention and 4-week follow-up. During the follow-up duration, the subject will receive standard rehabilitation program.

**Table 1 Tab1:** Experimental intervention as per the type of sensory impairment and motor recovery stage of the hand

Sensory Impairment	Level of therapy	Motor Recovery Stage			
		BRS-H 1 & 2	BRS-H 3	BRS-H 4	BRS-H 5 & 6
**Light touch**	**Level-I**	MT (unilateral) – cotton / wool /soft toy	MT (bimanual) – cotton / wool /soft toy	MT (bimanual) – grasp-release, lateral prehension-release using cotton / wool /soft toy	MT (bimanual) – grasp and release, prehensile activity using cotton / wool /soft toy
	**Level-II**	Bilateral and unilateral perception of cotton / wool / soft toy (therapist applied)	Bilateral and unilateral perception of cotton / wool / soft toy	Bilateral and unilateral perception of cotton / wool / soft toy by grasp-release, lateral prehension and release	Bilateral and unilateral perception of cotton / wool / soft toy by prehensile activity
	**Level-III**	Bilateral movements of upper limb joints holding cotton /wool /soft toy	Unilateral movements of upper limb joints holding cotton /wool /soft toy	Unilateral perception of cotton / wool / soft toy by grasp-release, lateral prehension and release	Unilateral movement (constraining the non-paretic limb) for prehensile activity using cotton / wool /soft toy
	**Level-IV**	Bilateral functional tasks – lifting cloth / pillow	Unilateral functional tasks – lifting cloth / pillow	Unilateral functional tasks – grasp-release, lateral prehension and release of cloth / pillow	Unilateral functional tasks (constraining the non-paretic limb) – grasp-release, lateral prehension and release of cloth / pillow
**Pressure**	**Level-I**	MT (unilateral) - clay (graded resistance) activity, ball squeezing	MT (bimanual) - clay (graded resistance) activity, ball squeezing	MT (bimanual) – grasp-release, lateral prehension and release of - clay (graded resistance) activity, ball	MT (bimanual) – pinching clay (graded resistance) activity
	**Level-II**	Bilateral and unilateral perception of clay (graded resistance) activity, ball squeezing (therapist applied)	Bilateral and unilateral perception of clay (graded resistance) activity, ball squeezing	Bilateral and unilateral perception of– grasp-release, lateral prehension and release - clay (graded resistance) activity, ball	Bilateral and unilateral perception of pinching clay (graded resistance) activity
	**Level-III**	Bilateral movements of upper limb joints holding high- density foam cylindrical blocks	Unilateral movements of upper limb joints holding high- density foam cylindrical blocks	Unilateral movements of grasp-release, lateral prehension and release - high- density foam blocks	Unilateral movement (constraining the non-paretic limb) for pinching clay (graded resistance) activity
	**Level-IV**	Bilateral movements of upper limb joints holding textured water glass/bottle	Uilateral movements of upper limb joints holding textured water glass/bottle	Unilateral movements of grasp-release, lateral prehension and release - textured water glass/bottle, key, cardboard	Unilateral functional tasks (constraining the non-paretic limb) – pinching and picking grains/coins
**Pin prick**	**Level-I**	MT (unilateral)– Scrubber / Steel wool/Velcro (rough)	MT (bimanual) – Scrubber / Steel wool/Velcro (rough)	MT (bimanual)– grasp-release, lateral prehension and release of Scrubber / Steel wool/Velcro (rough)	MT (bimanual)– prehensile activity using Scrubber / Steel wool/Velcro (rough
	**Level-II**	Bilateral and unilateral perception of Scrubber / Steel wool/Velcro (therapist applied)	Bilateral and unilateral perception of Scrubber / Steel wool/Velcro	Unilateral perception of grasp-release, lateral prehension and release of Scrubber / Steel wool/Velcro	Unilateral perception of prehensile activity of items textured with Scrubber / Steel wool/Velcro
	**Level-III**	Bilateral movements of upper limb joints holding textured (Scrubber / Steel wool/Velcro) cylindrical blocks	Unilateral movements of upper limb joints holding textured (Scrubber / Steel wool/Velcro) cylindrical blocks	Unilateral movements of upper limb joints comprises grasp-release, lateral prehension and release of textured (Scrubber / Steel wool/Velcro) blocks	Unilateral movements (constraining the non-paretic limb) of upper limb joints comprises prehensile activity of items textured with Scrubber / Steel wool/Velcro
	**Level-IV**	Bilateral movements of upper limb joints holding textured (Scrubber / Steel wool/Velcro) water glass/bottle	Unilateral movements of upper limb joints holding textured (Scrubber / Steel wool/Velcro) water glass/bottle	Unilateral movements of grasp-release, lateral prehension and release of textured (Scrubber / Steel wool/Velcro) daily use items	Unilateral movement (constraining the non-paretic limb) of prehensile activity of daily use items textured with Scrubber / Steel wool/Velcro
**Sharp-blunt discrimination**	**Level-I**	MT (unilateral)- Dellon’s Discriminator disc (therapist applied)	MT (bimanual) - Dellon’s Discriminator disc (therapist applied)	MT (bimanual) – sharp and blunt textured items alternatively	MT (bimanual) – prehensile activity of sharp and blunt textured items
	**Level-II**	Bilateral and unilateral sharp and blunt discrimination (therapist applied)	Bilateral and unilateral sharp and blunt discrimination	Unilateral sharp and blunt discrimination	Unilateral prehensile activity of sharp and blunt textured items
	**Level-III**	Bilateral movements of upper limb joints holding dual spikes/textured (blunt and sharp) cylindrical blocks	Unilateral movements of upper limb joints holding dual spikes/textured (blunt and sharp) cylindrical blocks	Unilateral movements of upper limb joints comprises sharp and blunt textured items along with manipulation; grasp-release, lateral prehension and release	Unilateral movements (constraining the non-paretic limb) of upper limb joints comprises prehensile activity of sharp and blunt textured items
	**Level-IV**	Bilateral movements of upper limb joints holding dual spikes/textured (blunt and sharp) water glass/bottle	Unilateral movements of upper limb joints holding dual spikes/textured (blunt and sharp) water glass/bottle	Unilateral sharp and blunt textured daily use items manipulation; grasp-release, lateral prehension and release	Unilateral movements (constraining the non-paretic limb) of upper limb joints comprises prehensile activity of sharp and blunt textured daily use items
**Proprioception**	**Level-I**	MT (unilateral)- task-based movements of shoulder, elbow, wrist; Movement of non-paretic upper limb and perceiving the limb position and movement with vision occluded.	MT (bimanual) - task-based movements of shoulder, elbow, wrist; Movement of the upper limbs and perceiving the limb position and movement with vision occluded.	MT (bimanual) - task-based movements of shoulder, elbow, wrist, hand, thumb and fingers; Movement of the joints and perceiving the limb position and movement with vision occluded.	MT (bimanual) - task-based movements of all upper limb especially fingers; Movement of the joints and perceiving the finger position and movement with vision occluded.
	**Level-II**	Bilateral movements of shoulder, elbow, wrist with visual feedback followed by vision occluded	Unilateral movements of shoulder, elbow, wrist with visual feedback followed by vision occluded	Unilateral movements of shoulder, elbow, wrist hand, thumb and fingers; with visual feedback followed by vision occluded	Unilateral movements (constraining the non-paretic limb) of all upper limb especially fingers; with visual feedback followed by vision occluded
	**Level-III**	Bilateral activity-based movements of shoulder, elbow, wrist with visual feedback followed by vision occluded	Unilateral activity-based movements of shoulder, elbow, wrist with visual feedback followed by vision occluded	Unilateral activity-based movements of shoulder, elbow, wrist hand, thumb and fingers; with visual feedback followed by vision occluded	Unilateral activity based movements (constraining the non-paretic limb) of all upper limb especially fingers; with visual feedback followed by vision occluded
	**Level-IV**	Bilateral functional task-based movements of shoulder, elbow, wrist with visual feedback followed by vision occluded	Unilateral functional task-based movements of shoulder, elbow, wrist with visual feedback followed by vision occluded	Unilateral functional task-based movements of shoulder, elbow, wrist, hand, thumb and fingers; with visual feedback followed by vision occluded	Unilateral functional task-based movements (constraining the non-paretic limb) of all upper limb especially fingers; with visual feedback followed by vision occluded
**Stereognosis**	**Level-I**	MT (unilateral) – 10 objects	MT (bimanual) – 10 objects; similar objects on both the sides.	MT (bimanual) – 10 objects; similar objects on both the sides; manipulation of objects by grasp-release, lateral prehension and release	MT (bimanual) – 10 small objects such as beads; similar objects on both the sides along with the manipulation of objects
	**Level-II**	Perceiving the 10 objects bilaterally with visual feedback followed by vision occluded	Perceiving the 10 objects unilaterally with visual feedback followed by vision occluded	Perceiving the 10 objects unilaterally with visual feedback followed by vision occluded; manipulation of objects by grasp-release, lateral prehension and release	Perceiving the 10 small objects unilaterally with visual feedback followed by vision occluded
	**Level-III**	Bilateral manipulation (reaching, lifting, placing) of 10 objects with visual feedback followed by vision occluded	Unilateral manipulation (reaching, lifting, placing) of 10 objects with visual feedback followed by vision occluded	Unilateral manipulation (reaching, lifting, placing, grasp-release, lateral prehension and release) of 10 objects (mixed together) with visual feedback followed by vision occluded	Unilateral manipulation (reaching, lifting, placing, in-hand manipulation) of 10 small objects (mixed together) with visual feedback followed by vision occluded
	**Level-IV**	Bilateral manipulation (reaching, lifting, placing) of variety of daily use items with visual feedback followed by vision occluded	Unilateral manipulation (reaching, lifting, placing) of variety of daily use items with visual feedback followed by vision occluded	Unilateral manipulation (reaching, lifting, placing, grasp-release, lateral prehension and release) of 10 daily use items (mixed together) with visual feedback followed by vision occluded	Unilateral manipulation (reaching, lifting, placing, in-hand manipulation) of 10 small daily use objects (mixed together) with visual feedback followed by vision occluded

*BRS-H* Brunnstrom Recovery Stage – Hand, *MT* Mirror therapy

#### Control group intervention

The control group will be provided same duration of standard rehabilitation program. The intervention will comprise of mirror therapy (movement based), motor therapy for the upper limb (utilizing activities such as pegs, blocks, pyramids, ball, and simulated sanding), and constraint–induced movement therapy. All the maneuvers will primarily comprise of motor tasks.

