**Methods:**

We propose to recruit 122 poststroke subjects in a randomized controlled, assessor blinded trial to be conducted in a rehabilitation-institute. The key eligibility criteria is age between 20 to 80 years, hemiparesis (right or left), ischemic or hemorrhagic stroke, 1 to 12 months poststroke, and impairment in any of the sensory modalities. The participants in the experimental group will receive **NE**uroplasticity-**P**rinciples-based **SE**nsory-**R**ehabilitation (**NEPSER**) protocol comprising active, repetitive, and meaningful training of the specific sensory modalities utilizing visuo-perceptual, cognitive, motor, and functional tasks will be imparted for 8 weeks, 5 sessions / week, each of 2 h. The control subjects will undergo only standard rehabilitation based on neurophysiological, biomechanical, and rehabilitative approaches. All the participants will be assessed for motor (Fugl-Meyer assessment, upper extremity section) and sensory recovery [Nottingham Sensory assessment (Erasmus MC modification of the revised version)] at baseline, 8-week, and 12-week follow-up. The Semmes weinstein monofilament, two-point discrimination test and modified rankin scale (disability) will be applied as secondary measures. A repeated-measures 2-way ANOVA will be used to estimate difference for the post intervention and follow-up scores between the groups.

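### Equal treatment duration is claimed for the control arm, but only the experimental arm has a 2–3 h home programme, and the session-length figures do not fit all eligible patients

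*Protocol article*

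**What the plan says.** All places are in the protocol article.

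- **Control arm.** Control group intervention states: "The control group will be provided same duration of standard rehabilitation program". It lists movement-based mirror therapy, upper-limb motor activities and constraint-induced movement therapy, and adds: "All the maneuvers will primarily comprise of motor tasks". It gives no hours, number of sessions, home practice or log.
- **Experimental arm, supervised.** Experimental group intervention states: "The regime will be imparted for 40 sessions, each 2 h, 5 sessions / week across 2 months". The Methods paragraph of the Abstract agrees: "will be imparted for 8 weeks, 5 sessions / week, each of 2 h".
- **Experimental arm, home.** A list introduced by "The following guidelines will be utilized while executing the experimental intervention" includes a home programme of touching meaningful objects that "will be provided throughout the day for 2–3 h during the entire 8-week", monitored by a log book kept by the patient or caretaker.
- **Within a session.** The same list states: "Maximum duration of the protocol will be 120 min with 20–25 min for each sensory modality with maximum of 5 min for each level". Where a modality is unimpaired, "the training time for that modality will be equally distributed to other impaired ones, with a maximum of 40 min for each". A two-minute rest follows each modality.
- **Who is trained in what.** Table 1 covers six modalities, each at four levels of therapy. Under Eligibility criteria, impairment of any one sensory modality is enough for entry.

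**The concern.** A statement that the control arm matches the experimental arm in duration tells the reader that the arms differ in content and not in amount. The experimental list undoes this by adding daily home practice that the control section does not mirror.

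Amount of practice matters in this trial by the authors' own account. The Introduction counts repetition, frequency and intensity among the principles of neuroplasticity, and faults two earlier trials for providing only 16 h and 10 h of therapy. The home programme is use of the hand with objects, so it could plausibly move both primary measures, FMA-UE and Em-NSA. If the trial is positive, a reader relying on matched duration would credit the sensory content when extra hours are an equally available explanation.

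The second issue is internal consistency. Session length is given once as a fixed 2 h and once as a 120-min maximum built from minutes per modality. For some eligible patients these cannot both be met, so the amount that the control arm is meant to match is itself unclear.

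**Working it through.** **1. The plan's own figure.** Sessions = 8 weeks × 5 per week = 40. Supervised hours = 40 × 2 h = 80 h. This reproduces the stated course.

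**2. Home programme.** Hours = days × 2 to 3 h. Days per week are not given, so both 7 and 5 are shown.

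| Assumed days/week | Days in 8 weeks | Home hours | Home ÷ 80 h | Home + 80 h |
|---|---|---|---|---|
| 7 | 8 × 7 = 56 | 112–168 | 1.4–2.1 | 192–248 |
| 5 | 8 × 5 = 40 | 80–120 | 1.0–1.5 | 160–200 |

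For a patient who receives full 2-h sessions, home practice at least equals the supervised time on every row. Planned total time is 160/80 = 2.0 to 248/80 = 3.1 times an 80-h control course. That ratio assumes that controls receive 80 h and no home practice, that the home programme is fully carried out, and that an hour at home counts the same as an hour with a therapist.

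**3. Session length by number of impaired modalities, k.** Let the maximum under the cap be min(120, 40 × k) minutes, and the default time be k × 20 to k × 25 minutes.

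| k | Maximum under the 40-min cap | Compared with a 2-h session |
|---|---|---|
| 1 | 40 min (40 × 40 / 60 = 26.7 h over the course) | cannot reach 2 h |
| 2 | 80 min (40 × 80 / 60 = 53.3 h over the course) | cannot reach 2 h |
| 3 | 3 × 40 = 120 min | can reach 2 h |
| 4 | 120 min at 30 min each | can reach 2 h |
| 5 | 120 min at 24 min each | can reach 2 h |
| 6 | default 6 × 20 = 120 to 6 × 25 = 150 min | fits only at 20 min each |

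If the two-minute rests come on top of the modality times, six modalities take 120 + 12 = 132 to 150 + 12 = 162 min.

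**4. Levels.** Four levels at no more than 5 min give 4 × 5 = 20 min per modality, which matches the low end of the default slot but not 25 or 40 min.

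**The case against.** Several arguments on the other side have force.

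- **A condensed article may omit control-arm detail.** Control hours or home advice could stand in the full protocol. That is possible, but the point does not rest on silence. The article affirms equal duration, describes the experimental home programme down to its log book, and describes the control arm down to pegs and blocks. The affirmed equality does not follow from what is printed.
- **Intensity is part of NEPSER.** Aim of the trial asks about the effectiveness of the protocol and names frequency and intensity as key aspects. Perspective calls them crucial components. This stands: comparing a more intensive package with standard rehabilitation is a legitimate design. It is not a duration-matched comparison, and should not be described as one.
- **A reader might infer that sessions can never be 2 h.** The figures do not support that. Three to five modalities can reach 120 min, and so can six at 20 min each if rest is included.
- **The 132–162 min total may double-count rest.** The sentence that sets the 120-min maximum already mentions intermittent rest. Only six modalities at 25 min necessarily exceed the maximum.
- **The 5-min limit per level may apply only to the default slot.** The 40-min cap comes in the next sentence, as an exception for unimpaired modalities. This calls for clarification and is not a firm contradiction.
- **A reader might infer that patients with one or two impaired modalities get less supervised time than controls, diluting the effect.** That assumes a fixed 80 h for every control. The equality statement could instead mean matching whatever the experimental arm receives.

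**Conclusion.** The point holds in two limited parts.

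First, as printed, the equal-duration claim can be true at most of supervised sessions. The experimental arm alone has a planned home programme of 112–168 h (7 days a week) or 80–120 h (5 days a week) beyond 80 supervised hours. A difference in FMA-UE or Em-NSA therefore cannot be attributed to sensory content rather than amount of practice. The size rests on the unstated days per week and on full adherence. The 2.0 to 3.1 ratio of total time is an illustration under the assumptions listed with it, not a figure from the plan.

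Second, the session figures conflict for identifiable eligible patients: at most 40 or 80 min with one or two impaired modalities against a stated 2 h, and 150 min with six modalities at 25 min against a 120-min maximum. This does not extend to three to five modalities, and it is separate from the home-programme imbalance.

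Neither part makes the trial invalid. Together they limit what a positive result can be said to show.

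**What to change.** 1. Reconcile the Abstract, the Experimental group intervention section and the Control group intervention section so that session length, time per modality and home practice agree and are stated for both arms. Which schedule applies is for the investigators to decide.
2. Unless total time is equal by design, limit the equal-duration statement to supervised sessions, and word the conclusion as the NEPSER package, including its home programme, against standard rehabilitation.
3. Record supervised minutes and home-practice hours in both arms, and report them by arm beside the primary results. The existing log book asks about sensory-functional use, so controls need a neutral log that does not prompt sensory practice.

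**Cost.** The changes need new wording, place a small recording burden on control patients, and narrow the conclusion. Recruitment began in October 2019 according to Perspective, so control participants already treated will have no home-practice log, and the report should say so.
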